## Exclusion criteria

1. Persons who are participating in a clinical study or have participated in a clinical study within the last 30 days (participation is based on the date of final investigational product administration).
2. Persons with a history of abuse of alcohol or other drugs within 6 months prior to screening.
3. Persons who drink 21 standard drinks or more per week (generally, 55 mL of soju is equated to 200 mL of beer or 30 mL of spirits).
4. Persons with a history of peptic ulcer disease with complications (bleeding, perforation, penetration, and gastric outlet obstruction) within the last 5 years.
5. Persons with a history of peptic ulcer disease without complications within 6 months prior to screening visit or persons with active peptic ulcer disease.
6. Persons who have been infected with helicobacter but did not undergo eradication therapy.
7. Persons with a known history of gastroesophageal reflux disease.
8. Persons with a confirmed diagnosis or clinical suspicion of the following arthropathies that may affect safety and efficacy evaluation: septic arthritis, inflammatory arthropathy such as rheumatoid arthritis, gout, recurrent pseudopain, Paget’s disease, fracture, ochronosis, acromegaly, hemochromatosis, Wilson’s disease, primary osteomalacia, and Ehlers Danlos Syndrome and other genetic collagen disorders.
9. Persons with surgery planned during the study period.
10. Persons with a history of gastrointestinal cancer.
11. Persons with a GI disorder due to a malfunction in drug absorption.
12. Persons with gastrointestinal bleeding, cerebrovascular bleeding, other bleeding disorders, or severe hematological disorders.
13. Persons with moderate to severe hepatic impairment (Child Pugh Class II or higher).
14. Persons with a history of severe heart failure or coronary artery bypass graft (CABG).
15. Persons with severe renal impairment (CrCl <30 mL / min).
16. Persons with severe hypertension (SBP ≥160 mmHg or DBP ≥100 mmHg) refractory to treatment.
17. Persons with a history of allergy to components of the investigational product.
18. Persons with hypersensitivity or allergy to other NSAIDs or PPIs.
19. Subjects who received contraindicated drug or therapy within a pre-specified period prior to study participation (Section 5.3.2).
20. Patients who are receiving contraindicated co-administration drug (Section 5.3.3).
21. Patients who have a history of surgery on the osteoarthritic joint within the past 1 year.

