## Contraindications for the control drug

1. Patients with hypersensitivity or a history of hypersensitivity to this drug or its components.
2. Patients with an allergic reaction to sulfonamides.
3. Patients with a history of asthma, acute rhinitis, nasal polyps, angioedema, urticaria, or allergic reaction to aspirin or other NSAIDs (including COX-2 inhibitors).
4. Patients with severe hepatic impairment.
5. Patients with severe renal impairment (CrCl <30 mL / min).
6. Patients with active peptic ulcer disease or GI bleeding.
7. Patients with inflammatory bowel disease, such as Crohn’s disease or ulcerative colitis.
8. Patients with congestive heart failure (NYHA II-IV).
9. Patients with confirmed ischemic heart disease, peripheral arterial disease, and / or cerebrovascular disease.
10. Pregnant women, or women of childbearing age.
11. Lactating women.
12. Patients being treated for post-carotid arterial bypass graft (CABG) pain.
13. Patients with hyperkalemia.
14. This drug contains lactose. Therefore, patients with genetic conditions such as galactose intolerance, Lapp lactase deficiency, or glucose-galactose malabsorption should not be given this drug.

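### The exclusion criteria omit or narrow three clinically important celecoxib contraindications that the protocol lists: sulfonamide allergy, NYHA II-IV heart failure and established cardiovascular disease

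*Protocol*

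**What the plan says.** Section 4.1 (Subjects) defines the study population as consenting osteoarthritis patients who satisfy the inclusion criteria and none of the exclusion criteria. On cardiac disease other than hypertension, exclusion criterion 14 in section 4.3.2 removes "Persons with a history of severe heart failure or coronary artery bypass graft (CABG"). Criterion 12 removes cerebrovascular bleeding, criterion 17 allergy to components of the investigational product, and criterion 18 allergy to other NSAIDs or PPIs. Criteria 19 and 20 point only to the drug lists in 5.3.2 and 5.3.3. No criterion points to the contraindication list for celecoxib.

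That list, section 5.3.5.2, has 14 items. Those that matter here are:

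- item 2: "Patients with an allergic reaction to sulfonamides"
- item 7: "Patients with inflammatory bowel disease"
- item 8: "Patients with congestive heart failure (NYHA II-IV")
- item 9: "Patients with confirmed ischemic heart disease, peripheral arterial disease, and / or cerebrovascular disease"
- item 13: "Patients with hyperkalemia"

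**The concern.** The eligibility rules and the control-drug contraindications are two lists in one protocol, and they should agree. Where the first is narrower than the second, a site can enrol a contraindicated patient without committing an eligibility violation.

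The design makes screening the main safeguard. Allocation is double-blind and 1:1 (7.2). No visit is scheduled between Day 1 and about Day 84 (6.1), and there is no data safety monitoring committee (1.4). Subjects are aged 50 or over, and low-dose aspirin is allowed before and during the study (5.3.2, 5.3.3), so patients with established cardiovascular disease are plausible recruits. Section 5.3.5.3 warns of potentially fatal thrombotic events, infarction and stroke with celecoxib, with a possibly higher risk in patients with cardiovascular disease. Section 5.3.5.4 (general precautions, no. 11) describes celecoxib as a sulfonamide that can cause fatal skin reactions.

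**Working it through.** No arithmetic in the plan bears on this point. The check sets each item of 5.3.5.2 against the 23 exclusion criteria.

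| 5.3.5.2 item | Nearest criterion in 4.3.2 | Coverage |
|---|---|---|
| 1 hypersensitivity to the drug | 17 | met |
| 2 sulfonamide allergy | none (17 and 18 do not reach other sulfonamides) | none |
| 3 allergic-type reaction to aspirin/NSAIDs | 18 | met |
| 4 severe hepatic impairment | 13 | met |
| 5 severe renal impairment | 15 | met |
| 6 active ulcer or GI bleeding | 5, 12 | met |
| 7 inflammatory bowel disease | none | none |
| 8 heart failure NYHA II-IV | 14 (severe only) | partial |
| 9 ischaemic heart, peripheral arterial, cerebrovascular disease | 14 (CABG history), 12 (cerebrovascular bleeding) | partial |
| 10 pregnancy or childbearing age | 22 (admits those using contraception) | partial |
| 11 lactation | 22 | met |
| 12 post-CABG pain | 14 | met |
| 13 hyperkalaemia | none | none |
| 14 galactose/lactase conditions | 11, at most | fragment |

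**Item 8.** Criterion 14 removes severe heart failure. NYHA II is within the contraindication, but a site would not ordinarily class it as severe, so it passes. The criterion matches the Naxozol contraindications (5.3.4.2, items 6 and 9), which are limited to severe cardiac failure and the period around CABG. It does not match the stricter celecoxib item.

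**Item 9.** Angina, prior infarction, stenting, ischaemic stroke and peripheral arterial disease all pass, because only CABG history and cerebrovascular bleeding are named.

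**Item 2.** The investigational product includes celecoxib (section 5), so criterion 17 removes a patient with known celecoxib allergy. It does not remove a patient who reacted to a different sulfonamide. Section 5.3.5.2 treats these as separate conditions, in items 1 and 2.

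**Items 7 and 13.** Neither has a criterion. Known hyperkalaemia might emerge from the history at Visit 1. Unrecognised hyperkalaemia would not, because the chemistry panel (Table 2; Appendix 1, footnote 6) is ALT, AST, BUN, creatinine, glucose and total bilirubin. Section 5.3.5.4 (general precautions, no. 25) says potassium must be monitored regularly in diabetic patients given celecoxib, and diabetic patients are not excluded. Measuring potassium would not be enough by itself: inclusion criterion 5 lets the investigator enrol subjects with laboratory values outside the reference range.

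**Exposure.** With 1:1 allocation, each contraindicated patient who is randomised has one chance in two of receiving celecoxib. The documents give no prevalence for any of these conditions, so no count follows.

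**The case against.** **Section 5.3.5 is not uniform.** The list of patients to be treated with caution in 5.3.5.4 includes heart failure (item 4) and cardiovascular disease (item 12), and general precaution no. 4 repeats the caution for heart failure. On that reading the protocol expects some such patients to be treated. This stands as a fact about the text, but a caution does not cancel a specific contraindication in the same section. It shows that sites need one clear rule.

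**Other safeguards exist.** Section 4.1 obliges the investigator to review eligibility carefully with the subject's health in mind. Medical history is taken, inclusion criterion 5 and exclusion criterion 23 allow a patient to be turned away, and 5.3.5.2 is in the investigator's hands. A reader might infer that contraindicated patients enter with no protection; these provisions show otherwise. The gap is a missing mandatory criterion. The provisions permit exclusion without requiring it, and several other contraindications were turned into explicit criteria (13, 15 and 18, for example).

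**The full tally overstates the problem.** A reader might infer from the table that half the celecoxib contraindications are unguarded. Seven of 14 items do lack full coverage, or six if contraception is accepted as meeting item 10, but they are not of equal weight. Item 10 affects few subjects at a minimum age of 50. Item 14 ("patients with genetic conditions such as galactose intolerance, Lapp lactase deficiency, or glucose-galactose malabsorption should not be given this drug") concerns rare conditions and may be caught in part by criterion 11 ("Persons with a GI disorder due to a malfunction in drug absorption").

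**Section 2.9 is not a false assurance about celecoxib.** It says the contraindications are already reflected in the criteria. Although section 5 defines the investigational product to include the control drug, 2.9 itself identifies the product it discusses as the Naxozol tablet.

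**Conclusion.** The concern holds for three contraindications: items 2, 8 and 9 of section 5.3.5.2. As written, 4.3.2 admits patients with these conditions to a trial in which half are assigned celecoxib. This should be corrected because it concerns patient safety and the protocol contradicts itself. Items 7 and 13, with the missing potassium test, are real gaps to close at the same time.

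The conclusion rests on reading the two lists literally and on taking severe heart failure to be narrower than NYHA II-IV. It does not depend on how many patients are affected, and no sample-size or error-rate figure in the plan depends on it. A reader might want to put a probability on at least one contraindicated patient receiving celecoxib; that would need a prevalence the documents do not supply.

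Some neighbouring mismatches are only consistency edits. Nelfinavir is missing from the lists in 5.3.2 and 5.3.3, but it is barred outright in 5.3.4.5, and 5.3.3 discourages all other drugs in principle. Section 4.2.6 says elderly anticoagulant users are excluded through the criteria and drug lists, yet none of these names anticoagulants; they are a caution or interaction warning, not a contraindication. Criterion 16 adds a requirement that severe hypertension be refractory, which 5.3.4.2 does not state but also does not define.

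**What to change.** In one protocol amendment:

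1. Widen criterion 14 to heart failure of NYHA class II-IV and to confirmed ischaemic heart, peripheral arterial or cerebrovascular disease, keeping the CABG clause.
2. Add allergic reaction to sulfonamides to 4.3.2.
3. Add inflammatory bowel disease and known hyperkalaemia to 4.3.2.
4. Add potassium to the chemistry panel in Table 2 and Appendix 1, using the blood already drawn at Visits 1 and 3, and state that hyperkalaemia at Visit 1 excludes the subject despite the laboratory allowance in inclusion criterion 5.

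In the same amendment, as minor edits: align criterion 22 with item 10, name the galactose and lactase conditions, list nelfinavir in 5.3.2 and 5.3.3, reconcile the anticoagulant sentence in 4.2.6 with the drug lists, and reconcile criterion 16 with 5.3.4.2.

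The cost is the amendment itself, one extra analyte and some extra screen failures, so enrolment may be somewhat slower. The sample size is unaffected.

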## Assignment of screening and subject numbers

A screening code number (S + site initial + XXX) will be assigned to each volunteer who has provided written consent to participate in the study in the order of their screening site visit. The screening code will start from S + site initial + 001 and will be assigned as a serial number. Once assigned, a screening code cannot be assigned to another subject, and each subject will receive only one screening code. Subjects participating in this study who successfully complete screening tests will undergo randomization to experimental or control groups on Day 1 and will receive a subject code number (R + site initial + XXX). The subject codes will start from RX001 at each site and will have a specific pattern. For example, in ‘RB006’, ‘R’ means randomized, ‘B’ is the site initial, and the three-digit number, ‘006’, means that this subject is the 6^th^ patient to be randomized at site B. Each subject code assigned to a subject will be used as the subject identification code until study termination. Once assigned, a subject code cannot be assigned to another subject. Each subject will receive only one subject code.

## Study group allocation

At the screening visit, a screening code will be assigned to each subject after written consent and successful completion of the screening tests. Subjects who fulfill the inclusion criteria will be assigned to a treatment at Visit 2. The subjects will be allocated to experimental or control groups, and the investigational products will be administered. After allocation, each subject will be assigned a subject code, generated by the sponsor, contract research organization, or persons entrusted by them for computer-based code generation. The assigned subject code will be recorded on the case report form, and the subject will be identified using age and the subject identification code for the remainder of the study. The subject code cannot be re-used during the study.

This study is a parallel-group study. The number of subjects allocated to the experimental and control groups is as follows:

#### Table 1. Treatment groups and number of subjects per group

|  | Dose | Number of subjects | Administered drug |
| --- | --- | --- | --- |
| Experimental | 1 tablet, twice a day | 53 | Naxozol tablet |
| Control | 1 capsule, once daily | 53 | Celebrex capsule |

## Subject withdrawal criteria

Withdrawal of a subject from the study, temporary discontinuation of investigational product administration, early termination of the study, or closure of a study site may occur due to personal, medical, or administrative reasons as listed below:

## Study withdrawal

A subject can withdraw from the study at any time and is not obliged to reveal the reason. A subject must be withdrawn from the study if one of the situations below arises:

- - Withdrawal of consent by the subject or the subject’s legal proxy.
  - The investigator’s assessment that continued participation in the study is harmful to the subject.
  - Adverse events too serious to continue the study (CTCAE grade 4 or 5) or difficulty with study participation as per the investigator’s assessment.
  - Serious protocol violation as per the sponsor or investigator’s assessment.
  - Unfit to continue in the study as per the sponsor or investigator’s assessment.
  - A subject’s wish to withdraw from the study for other reasons.

In cases of serious protocol violation as listed below, the corresponding subject must be excluded from the analysis (PP excepted):

- - Need for cessation of study participation due to the possibility of biasing the efficacy or safety evaluation of the experimental drug, or the violation of inclusion / exclusion criteria that can affect the safety of a subject, as per the investigator or sponsor’s assessment.
  - Notification by a subject of the use of another drug or treatment for the study’s target disease during the study period, and the investigator’s conclusion that the subject has no intention of ceasing the use of such drug or treatment.
  - The use or administration of drugs contraindicated for co-administration with the investigational product, as stated in Section [5.3.3](#_bookmark68).
  - Subjects who did not undergo washout for specified drugs before randomization.
  - Incorrect randomization.
  - Less than 80% compliance rate.

If the follow-up of a withdrawn subject is not possible, the investigator must make an effort to confirm the address and health status of subject. If a subject is withdrawn from the study, all efforts must be made to record, in full detail, the reason and situation leading to their withdrawal. If a subject withdraws early, the evaluation and treatment corresponding to Visit 3 must be conducted, when possible in addition to an appropriate assessment to determine the reason for early withdrawal, including any adverse reactions to the investigational products (refer to Section 6.1). The reason for withdrawal must be recorded in case report form for all cases.

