## Drugs or therapies contraindicated during study participation

Drugs other than investigational products, especially one of the drugs listed below, should not be administered during the study period, on principle:

1. NSAIDs (LDA [<325 mg/day low dose aspirin] excluded) other than investigational products.
2. Other gastroprotective drugs (H2 blockers, PPIs, misoprostol, etc.).
3. IV or oral corticosteroids (oral corticosteroids corresponding to ≤7.5 mg / day prednisone, topical ointments, eyedrops, nasal agents excluded).
4. Intraarticular or intramuscular corticosteroids or hyaluronic acid.
5. Glucosamine and / or chondroitin sulfate.
6. Lithium.
7. Antiretrovirals (atazanavir, atazanavir sulfate).

All drugs deemed necessary by the investigator, as per the investigator’s medical opinion, can be given. However, if a drug administered without an investigator’s assessment is deemed to have the capacity to influence the safety and efficacy evaluation of this study, the corresponding subject will be excluded from PP analysis. All drugs administered, and their dosage, route of administration, and reason for administration, must be recorded in a case report form signed by the investigator.

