## Definition of analysis sets

#### Target population

This study will be conducted on osteoarthritis patients of ≥50 years who can perform normal physical activity during the study period, with a pain VAS of 40 mm or more.

**Safety evaluation set: A population in which at least one safety follow-up observation is made after randomization and investigational product administration.**

**Full Analysis (FA) set: A population in which at least one efficacy evaluation is performed after randomization and investigational product administration.**

**Per-Protocol (PP) set: A population in which at least one efficacy evaluation is performed after randomization and investigational product administration, and in which there is no major protocol violation (violation of inclusion / exclusion criteria, violation of compliance). A compliance rate of 80% is used as the reference.**

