## Statistical analysis plan

## General considerations

Efficacy data obtained from the subjects in this study will be analyzed in the FA and PP sets. Safety data will be analyzed in the Safety evaluation set. Considering that this is a non-inferiority study, the primary efficacy endpoint will be analyzed in both the FA and PP sets, according to ICH guidelines.

All statistical sets, excluding the primary efficacy endpoint, will be subjected to two-sided tests with a significance level of 5%.

Missing data will be replaced using a multiple imputation method. No interim analysis will be performed.

Co-administered drugs will be recorded in ATC terminology, and adverse events and medical history will be standardized to SOC (system organ class) and PT (preferred term) using a Medical Dictionary (MedDRA or WHOART).

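### Section 4.5.1 ends follow-up of serious protocol violators before week 12 and, read literally, drops them from the full analysis set instead of the per-protocol set

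*Protocol*

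**What the plan says.** **Withdrawal.** Section 4.5.1 makes withdrawal from the study obligatory when a listed situation arises: "A subject must be withdrawn from the study if one of the situations below arises". The list includes "Serious protocol violation as per the sponsor or investigator’s assessment". The section then names the serious violations: eligibility breaches or other need to stop participation, use of another treatment for the target disease, prohibited drugs, missed washout, incorrect randomization, and compliance below 80%.

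**Analysis.** For those violations 4.5.1 adds that "the corresponding subject must be excluded from the analysis (PP excepted"). Section 7.4 puts in FA anyone with at least one efficacy evaluation after randomization and dosing. PP is the narrower set, with one further condition: "and in which there is no major protocol violation (violation of inclusion / exclusion criteria, violation of compliance"). Section 7.5.1 states that "the primary efficacy endpoint will be analyzed in both the FA and PP sets, according to ICH guidelines", and that missing data are multiply imputed.

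**Data at exit.** Section 4.5.1 provides: "If a subject withdraws early, the evaluation and treatment corresponding to Visit 3 must be conducted, when possible". The early termination visit in 6.1 lists the LDQ. Section 4.9 says no further evaluation follows termination.

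**Prohibited drugs.** Section 5.3.3 says that, where a drug given without the investigator's assessment could influence the evaluation, "the corresponding subject will be excluded from PP analysis".

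**The concern.** In a non-inferiority trial, FA guards against a PP result produced by removing off-protocol subjects. It can do so only if it holds those subjects' outcomes at the planned time. The protocol separates stopping study drug (4.5.2) from leaving the study (4.5.1), yet it places serious violations among the grounds for leaving. A violator who is willing to attend Visit 3 is sent out early, and the week-12 LDQ is lost by rule.

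The loss may be related to outcome. The prohibited drugs include acid suppressants and other NSAIDs, and subjects may take them because of dyspepsia or pain. The exclusion sentence adds a second problem: anyone applying it as written would take violators out of FA and leave them in PP.

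**Working it through.** **1. The plan's sample size.** From 7.1: margin 0.40, SD 0.65, one-sided α 0.025, power 80%.

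n per arm = 2 × 0.65² × (1.96 + 0.842)² / 0.40² = 0.845 × 7.851 / 0.16 = 41.5, rounded up to 42. Then 42 / 0.8 = 52.5, rounded up to 53 per arm, 106 in total. Both figures reproduce.

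**2. Is this a power problem?** Power at a true difference of 0 is Φ(0.40 / (0.65√(2/n)) − 1.96). It is 88.7% at n = 53, 85.4% at 48 and 80.5% at 42. Withdrawals within the planned 20% are covered in number. The issue is bias and the value of FA as a check.

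**3. What happens to a violator under the text.**

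| Case | Week-12 LDQ | FA under 7.4 | PP under 7.4 | 4.5.1 sentence, literally |
|---|---|---|---|---|
| Found before Day 84, exit LDQ taken | none | in, on an early or imputed value | out if a major violation | out of FA, in PP |
| Found before Day 84, no exit LDQ | none | out (no post-dose efficacy evaluation) | out | out of FA, in PP |
| Found at Visit 3 | taken | in | out if a major violation | out of FA, in PP |

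The LDQ is scheduled only at Visits 2 and 3 and asks about the last four weeks. An exit LDQ therefore describes the four weeks before exit, not weeks 8 to 12. With no scheduled LDQ between baseline and Visit 3, imputation has little post-baseline information to use.

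**4. Possible size (assumed rates; the protocol gives none).** Simulated normal LDQ changes, 53 per arm, SD 0.65, true difference at the margin of 0.40. Subjects are removed on a latent score correlated ρ with LDQ worsening, and the pooled-variance upper 97.5% limit is compared with 0.40.

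Removing a fraction p lowers an arm's mean by ρ × 0.65 × φ(z) / (1 − p), where z is the normal quantile at 1 − p. With ρ = 0.6:

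- p = 0.05: 0.39 × 0.1031 / 0.95 = 0.042
- p = 0.10: 0.39 × 0.1755 / 0.90 = 0.076
- p = 0.15: 0.39 × 0.2332 / 0.85 = 0.107

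The expected difference is 0.40 − (0.076 − 0.042) = 0.366 at 10% v 5%, and 0.40 − (0.107 − 0.042) = 0.335 at 15% v 5%. Simulation agrees. Chance of declaring non-inferiority, nominally 2.5%:

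| Withdrawn, Naxozol v celecoxib | Assumption | Chance |
|---|---|---|
| 10% v 10% | ρ = 0.6, deleted | about 2.5% |
| 10% v 5% | ρ = 0.6, deleted | about 4.5% |
| 15% v 5% | ρ = 0.6, deleted | about 7.5% |
| 10% v 5% | ρ = 0.3, deleted | 3.0–3.4% |
| 15% v 5% | ρ = 0.3, deleted | 4.2–4.3% |
| 5% v 10% | ρ = 0.6, deleted | about 1.3% |
| 5% v 15% | ρ = 0.6, deleted | 0.6–0.7% |
| 10% v 5% | ρ = 0.6, exit LDQ used, correlated 0.7 with week 12 | about 2.9% |
| 15% v 5% | as above | 3.2–3.5% |

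Ranges are the spread between repeat runs. With ρ = 0 there is no inflation. The deletion rows ignore both the exit LDQ and multiple imputation, so they do not represent the protocol's analysis.

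**The case against.** - **FA membership.** Withdrawal alone does not remove a violator from FA, since 7.4 needs only one post-dose efficacy evaluation and an exit LDQ is required when possible. This stands.
- **Late detection.** No visit is scheduled between Day 1 and Day 84, so a prohibited drug taken on treatment will often surface only at Visit 3, when the week-12 LDQ is taken. Compliance is counted from returned product, so the same applies. This stands for many cases but not all: 4.5.1 itself foresees a subject reporting other treatment during the study, and eligibility, washout and randomization errors can be found early.
- **Balance.** Errors that predate treatment have no reason to differ between arms in a double-blind trial, and equal withdrawal gives about the nominal error rate. This stands, and it limits the likely bias.
- **Benefit of follow-up.** If a prohibited acid suppressant lowers the LDQ by an assumed 0.40 to 0.65, following everyone also narrows the observed difference. Non-inferiority is then declared 3.5–4.5% of the time at 10% v 5%, and 5.0–7.8% at 15% v 5%. So the simulation does not show that follow-up lowers the error rate. The reason to follow is to have the outcome as randomized instead of a gap.
- **Contradiction with other sections.** Sections 5.3.3, 6.4.2 and 7.4 say who belongs in PP. None says that violators stay in follow-up, so being withdrawn and being outside PP are compatible. This stands. The direct conflict is between the 4.5.1 exclusion sentence and 7.4.

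**Conclusion.** The point holds in a limited form. Section 4.5.1 requires study withdrawal for a serious protocol violation. A violator identified before Day 84 then has no week-12 LDQ, and FA becomes a weaker check on PP. The exclusion sentence conflicts with 7.4 and must be reconciled with it whatever the number of violators.

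A reader might infer more: that FA loses these subjects altogether, that FA collapses into PP, or that the false non-inferiority rate rises to some 4.5% or 7.5%. The documents do not support this. A subject with an exit LDQ stays in FA, and violations found at Visit 3 still separate the two sets. The error rates rest on assumed unequal withdrawal and an assumed correlation, and with the arms reversed they fall below 2.5%. No violation rate is given, so size and direction are unknown, and the bias is small if violations are balanced. The case for change is that the missing data are avoidable at almost no cost.

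**What to change.** 1. In 4.5.1, remove serious protocol violation as an automatic ground for withdrawal from the study.
2. State that violators who still consent are followed to the scheduled Visit 3 and that the week-12 LDQ is taken.
3. Reconcile the exclusion sentence in 4.5.1 with 7.4, so that violators are analysed as randomized in FA and excluded only from PP. Without this step the first two do not work, because the sentence would still remove violators from FA.
4. Leave the safety and fitness grounds for withdrawal, including the ground of being unfit to continue, and decisions on study drug under 4.5.2, unchanged.

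Cost: a wording amendment and slightly more follow-up of off-protocol subjects, at a visit already planned for everyone.
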